## Methods

The following protocol (version 5, September 9th 2022) follows SPIRIT guidelines for reporting protocols (see Additional file 1). In this four-arm parallel-group RCT of SRG, MT and MiCBT versus an active control (equal allocation ratio), we will deliver the interventions to small groups of smokers to maximise the potential cost-effectiveness. 6-months of these interventions will be followed by 6-months of online peer support and a further 6-month follow-up period. The control group will be directed to optional resources including counselling (Quitline) and information about pharmacological aid. We aim to: (a) test the efficacy of the three interventions (SRG, MT and MiCBT) for smoking cessation and (b) levels of resilience in low SES groups and how this changes during exposure to the interventions, (c) measure the cost-effectiveness and cost-utility of the interventions in low SES groups, and (d) undertake a process evaluation of the different interventions in low SES groups. We hypothesise the following:H1: The proportion of participants who report 14-day period abstinence from smoking at 6 months will be significantly higher for each intervention group compared to the control group.H2: Amongst participants that report 14-day period abstinence at 6 months, the proportion of participants who report 14-day period abstinence at 12 months will be significantly higher for each intervention group compared to the control group.H3: The proportion of participants who report 14-day period prevalence abstinence from smoking at 6 months post-trial (18 months from baseline) will be significantly higher for each intervention group compared to the control group.H4: Levels of resilience measured by the Connor-Davidson CD-25 [43] and ENRICHD Social Support Inventory [44] will be significantly higher for each intervention group compared to the control group at 6, 12 and 18 months post randomisation.H5: The interventions will improve smoking cessation and QALYs at a reasonable and acceptable incremental cost.

In addition, we pose the following research questions for the qualitative component of the study (that pertains to the process evaluation):RQ1: Have the different interventions been implemented and received as intended?RQ2: What are the barriers and facilitators associated with the first research question?RQ3: For whom, and in what circumstance were the interventions effective (and cost-effective) or not, and why?

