#### Phase 1 (months 0–6): group-based interventions

Participants allocated to interventions will attend eight 1-h group sessions online via Zoom over a 6-month period according to a prescribed ideal delivery schedule. Participants will be asked to provide approval these sessions to be recorded (so that they may provide data for analysis regarding intervention delivery, as described above). The facilitators running the interventions will have formal qualifications in CBT and will receive specialised training from experts in mindfulness training and setting realistic goals.

To ensure that all participants are encouraged to access the current best practice approach to smoking cessation, the Royal Australian College of General Practitioner’s [65] “Ask, Advise, Help'” model for smoking cessation will be offered to all participants from baseline, including active control group participants. This approach involves referral to behavioural counselling and provision of information on accessing Nicotine Replacement Therapy and stop-smoking medications where indicated. The behavioural counselling offered in the current study is via the Quitline service.

##### Arm 1

MiCBT is a four-stage therapeutic approach. [66] Therapy begins at the personal stage, with the internal promotion of experiential awareness and acceptance. The second stage introduces imaginary and in vivo exposure procedures, and the third stage extends mindfulness principles into interpersonal interactions. Stage four, the empathetic stage, involves developing ethical awareness and compassion, which is intended to help prevent relapse through counterconditioning. The approach is based on *Vipassana* (insight training) and the co-emergence model of reinforcement. This model proposes that operant behaviour is reinforced by the interoceptive feedback (i.e., conscious or unconscious bodily sensation) which co-emerges with self-referential cognitions, rather than the environmental consequences posited by Skinner. [67] Participants undergoing MiCBT will also be asked to complete 30—60 min of homework daily, including mindfulness practice twice daily and some readings. Homework will be guided by a smartphone application.

##### Arm 2

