#### Analyses

All analyses will use Stata (version 17.0 [69]). This will be undertaken blinded to the participants’ group allocation. Mixed-effects modelling will be used to assess the effect of the interventions on primary and secondary outcomes. This approach accounts for the correlation of the data from repeat measures over time and reduces bias caused by missing data at one or more time points for each participant. In addition, we will develop prediction models to determine whether levels of internal and external resilience measured at baseline predict smoking cessation. As an exploratory analysis, we will also perform mediation analyses to determine the direct and indirect effects of the separate components of each intervention on the primary and secondary outcomes.

For outcomes assessed at a single time-point, we will assess the difference between the four groups at that time. For outcomes assessed at repeat time points, we will assess differences between the four groups at each time point, with adjustment for multiple comparisons. We will assess binary outcomes using mixed-effects logistic regression and continuous outcomes using linear mixed-effects regression. In repeated measures, we will treat time as a categorical variable, and the model will include fixed-effects for time and group. Subgroup analysis will be undertaken to test whether people with a critical level of resilience are more likely to stay quit than those that do not meet this level. The main analyses will be performed on a per-protocol basis. Our intention-to-treat population will be defined as all participants that were randomised and also completed the baseline survey. We will perform a sensitivity analysis on a modified intention-to-treat basis and impute missing data where possible. Where more than 10% of data are missing, we will also perform multiple imputation as a sensitivity analysis to account for possible bias in estimates caused by missing data. Missing smoking data will be presumed MNAR and analysed as continued smoking. Hypothesis testing will be performed using 2-tailed tests with a Type 1 error rate of alpha = 0.05, and 0.05/3 = 0.0167 when assessing each outcome across time to account for the repeated testing at 6, 12, and 18 months. We will make further adjustments for multiple comparisons (e.g., 3 comparisons with control) depending on each outcome.

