We anticipate several difficulties. Most notably, the interventions will be administered online rather than face-to-face due to social restrictions imposed by the COVID-19 pandemic. This constraint raises questions over the generalisability for face-to-face setting and accessibility to those without ready access to the internet. Nonetheless, testing the efficacy of the interventions in an online setting is important because it reflects real world changes in the way services are provided and supports the inclusion of geographically remote participants. There is evidence that online interventions are effective for addiction treatment (including smoking [70]), and furthermore, there is growing evidence that internet-based CBT can be equivalent to face-to-face CBT in treating a range of psychological problems. [71] Other potential problems raised by the online delivery are lower adherence with intervention protocols and higher drop-out rates. [72] We will try to improve adherence with text message reminders of session times and in-session reminders to complete homework. For the two mindfulness-based interventions, the addition of a recently developed smartphone application provides a simple and user-friendly access route that encourages the completion of homework. We will address the possible attrition bias by using a modified intention-to-treat analysis protocol, whereby participants who drop out of the study will continue to be followed for data collection purposes. We will only request data from participants who have completed the baseline survey.

To summarise, this study aims to test the efficacy of mindfulness and goal-setting interventions with low SES smokers. We will examine the practical application of the interventions to low SES smokers by performing a process evaluation and assessing cost-effectiveness and cost-utility. We expect that our assets-based approach to smoking cessation can guide future public health programs to reduce the prevalence of smoking-related health problems and ameliorate the socioeconomic inequities which continue to be associated with smoking.

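### The main analysis of a superiority trial is per-protocol, with modified intention-to-treat only as a sensitivity analysis, so the headline comparison rests on a post-randomisation subset

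*Protocol article*

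**What the plan says.** The first hypothesis (H1, Methods) is one of superiority: "abstinence from smoking at 6 months will be significantly higher for each intervention group compared to the control group". Under Analyses, the article sets the basis for testing it: "The main analyses will be performed on a per-protocol basis". It then defines another population, "Our intention-to-treat population will be defined as all participants that were randomised and also completed the baseline survey", and gives that kind of analysis a secondary role: "We will perform a sensitivity analysis on a modified intention-to-treat basis and impute missing data where possible". The same paragraph adds a rule for missing outcomes: "Missing smoking data will be presumed MNAR and analysed as continued smoking". No definition of the per-protocol population is given.

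The Discussion names lower adherence and higher drop-out as possible problems of online delivery. It continues: "We will address the possible attrition bias by using a modified intention-to-treat analysis protocol", and explains that people who drop out will still be followed.

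The arms differ in what they ask of participants. Under Phase 1, "Participants allocated to interventions will attend eight 1-h group sessions online via Zoom over a 6-month period". The MiCBT arm adds 30–60 "min of homework daily, including mindfulness practice twice daily and some readings", and the mindfulness training arm has a similar daily load. Controls are pointed to services that they may use or not, as they wish.

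**The concern.** Randomisation makes the arms comparable at the moment of allocation. A per-protocol set is chosen by what happens afterwards, so a difference between arms can reflect who was kept as well as what the intervention did. In a superiority trial this can produce a positive result with no true effect. Defining the per-protocol set later in an analysis plan would not cure this, because the problem is its role as the main analysis.

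The direction of the bias depends on the missing definition:

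- **If per-protocol depends on sessions or homework,** exclusions would fall mainly on the three intervention arms, because controls have almost nothing to fail to adhere to. If attendance is related to the chance of quitting, the bias favours the interventions.
- **If per-protocol means completing follow-up,** all four arms are selected, not necessarily alike, and the direction is unknown.

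The Discussion also relies on modified ITT to deal with attrition bias. That sits poorly with making it a sensitivity analysis, and a reader cannot be sure which result the conclusions will rest on.

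**Working it through.** **The plan's own figure.** Inputs from Sample size and power analysis: 13.6% (usual care) against 25.2% (mindfulness training), two-sided alpha 0.05, power 80%. With pooled variance under the null and mean rate 0.194:

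n = [1.960 × √(2 × 0.194 × 0.806) + 0.842 × √(0.136 × 0.864 + 0.252 × 0.748)]² / 0.116² = 181.2, rounded up to 182 per group.

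Allowing for 10% drop-out, 182/0.9 = 202.2, rounded up to 203, and 4 × 203 = 812. The stated numbers reproduce, so no arithmetic in the plan is in dispute.

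**Size of the bias under the null.** The documents give no adherence rate and no relation between adherence and quitting, so both are assumptions here. The true quit rate is 13.6% in both arms, 203 are randomised to each, all controls are kept, and only adherers are kept in the intervention arm. Let a be the proportion adherent and r the ratio of the quit rate in adherers to that in non-adherers.

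- Non-adherers: q_n = 0.136 / (a·r + 1 − a). Adherers: q_a = r·q_n.
- Rejection probability = Φ[(d − 1.96·se0)/se1] + Φ[(−d − 1.96·se0)/se1], where d = q_a − 0.136, se0 is the pooled and se1 the unpooled standard error, with 203 controls and 203a intervention participants.

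Worked case, a = 0.7 and r = 2:

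- q_n = 0.136/1.7 = 0.080, q_a = 0.160 and d = 0.024.
- With 203 against 142.1 participants, se0 = 0.0386 and se1 = 0.0390.
- The probability is Φ(−1.32) + Φ(−2.55) = 0.093 + 0.005 = 9.8%.

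| Adherent | Apparent intervention quit rate, r = 2 | False positives, r = 1.5 | r = 2 | r = 3 |
|---|---|---|---|---|
| 90% | 14.3% | 5.2% | 5.5% | 5.9% |
| 80% | 15.1% | 5.9% | 7.1% | 8.9% |
| 70% | 16.0% | 7.0% | 9.8% | 14.4% |
| 50% | 18.1% | 10.4% | 19.0% | 34.2% |

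**A second model.** Let a standard normal trait U drive both behaviours: logit P(quit) has slope 0.5 or 0.8 on U and averages 13.6%; logit P(adhere) has slope 0.5 or 1.0 and averages 50% or 70%. The apparent quit rate is the mean of P(quit) weighted by P(adhere). Over the eight combinations it runs from 14.4% to 17.2%. The false-positive rate runs from about 5.5% to 14%, whether 182 or 203 controls are used. In four of the eight combinations it stays below 7%.

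**ITT on the planned 203 per group.** Power at 25.2% against 13.6% is 84.3% with everyone observed. If 10% in each arm are missing and counted as smokers, the rates become 0.9 × 25.2% = 22.7% and 0.9 × 13.6% = 12.2%, and power is 79.3%. This assumes that those lost would have quit at their arm's rate. If instead non-attenders quit at the control rate, the intervention rate is 0.252a + 0.136(1 − a), and power is about 77%, 68% and 57% at 90%, 80% and 70% attendance.

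**The case against.** The strongest reply is that per-protocol is undefined here and its definition may properly sit in an analysis plan that is not shown. A reader might infer that the headline result will compare self-selected attenders with an unselected control arm. The article does not establish that. Under Ethical considerations it adds a control-arm lottery to limit differential drop-out, so losses among controls are expected too. This part of the objection stands, and the direction of the bias must be stated conditionally.

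The link between attendance and quitting is also an assumption. The Background ties motivation and self-efficacy to successful quit attempts, but no section ties them to session attendance. Eligibility is limited to smokers planning to quit, which may narrow the range of motivation.

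Three further readings go too far:

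- **Drop-outs both removed and counted as smokers.** The missing-as-smoking rule is not tied to a population. It could serve the modified ITT analysis, or an adherent participant who misses the 6-month survey.
- **A flat contradiction between Analyses and Discussion.** The Discussion does not call modified ITT the main analysis. The text is ambiguous and needs alignment.
- **A loss of power as an argument against per-protocol.** Per-protocol selection can raise the observed quit rate while it shrinks the sample, so its net effect on power is not known. Power can also fall under ITT.

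None of this reaches the core. The article says outright that the main analyses are per-protocol, and nothing elsewhere reverses it. Under either definition the primary comparison is on a post-randomisation subset.

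**Conclusion.** The point holds in this form: the main analysis of a superiority hypothesis is placed on a population formed after randomisation, and the analysis that would keep the randomised comparison is relegated to sensitivity. This should be changed before the data are analysed, because it governs the primary result.

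The size is uncertain. If exclusions fall only on intervention non-adherers, the false-positive rate is close to nominal at 90% adherence (5.2–5.9%). At 50–70% adherence it is about 5.5–14% in the shared-trait model and about 10–19% if adherers quit at twice the rate of non-adherers. These figures rest on assumed adherence rates and assumed links between adherence and quitting. They illustrate what could happen and do not predict this trial's error rate. If per-protocol means completing follow-up, they do not apply, and the remaining concern is selection of unknown direction in all arms.

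**What to change.** In the Analyses section:

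- **H1 and H3:** make the main analysis ITT by allocated arm, with missing smoking status counted as smoking.
- **H4:** analyse by allocated arm with the planned linear mixed model. Counting missing as smoking has no meaning for the resilience scales.
- **H2:** keep the stated subset of 6-month abstainers, by allocated arm and without adherence exclusions, and label it a non-randomised comparison, since membership depends on a post-randomisation outcome.
- **Per-protocol:** define it and report it as supportive.
- **Discussion:** align its statement on modified ITT with the Analyses section.
- **Baseline survey:** Screening and group allocation describes it after random allocation, while Timepoints places baseline measures before randomisation. Reconcile the two, so that the ITT set does not exclude people for something that happened after allocation. The Discussion limits data requests to those who completed this survey. Anyone randomised without it can still be counted as smoking for H1 and H3.

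The cost is a change of wording in the protocol and the registry entry. No new data are needed, because drop-outs who completed the baseline survey are already to be followed. The real downside is that the ITT estimate may be smaller, and power on 203 per group falls below 80% if non-attenders quit at the control rate. That prospect should be acknowledged when the change is made.

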#### Screening and group allocation

Prospective participants will complete an online screening questionnaire that addresses the inclusion criteria through Qualtrics. If eligible, they will be asked to give informed consent. Participants will be randomly allocated to one of the three interventions or a control group using computerised sequence generation within the Qualtrics survey (Mersenne Twister algorithm [64]). All participants will complete a baseline questionnaire (see Table 1). Intervention-group participants will then be divided in groups of between 2 and 7 participants within each of the intervention groups (MiCBT, MT, SRG) based on their availability for session times throughout the week.

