### Statistical analysis

#### Timepoints

All psychological and behavioural measures (internal resilience, external resilience, self-efficacy, motivation, stress, nicotine dependency, and goal achievement) will be measured before randomisation and then at 3 monthly intervals for the first 12 months (see Table 1; baseline goal assessment at 5 weeks). A final collection of data on these scales will occur at 18 months to test for maintenance of impacts. Equanimity will be measured at baseline, and then weeks 7, 13, 20, 52, and 78 after commencement of phase 1.

In addition to the primary outcome (cessation at 6-months), smoking cessation will be assessed at 4, 8, 12, 16, 20, 52, and 78 weeks to address hypotheses and to compare the trajectory of smoking cessation between groups.

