### Ethical considerations

There are several ethical considerations associated with this study. To promote an active control group in which the participants receive a usual standard of care, we have elected to expose all participants to the Royal Australian College of General Practitioners Ask, Advise, Help model. Furthermore, both control and SRG group participants will be offered free access to the mindfulness smartphone application after completing the study, should it prove to be of benefit. We also acknowledge that we are studying a vulnerable group. During the ongoing process evaluation, we will “check in” with participants who have dropped out of the interventions to explore how our procedures might be adapted to address any problems they encountered that led to their dropping out and facilitate positive changes in psychological wellbeing. Acknowledging the economic vulnerability of the participant group, we offer intervention group participants who are required to engage with the study via Zoom will be compensated for their data usage with $50 gift cards upon completion of the baseline survey and attendance at their first small group session. For participants who complete the 18-month study, a lottery will be drawn to randomly select winners of supermarket vouchers to the value of $300, $200 and $100. In addition, all control group participants who complete the study will be entered in a lottery to win 1 of 3 x $100 supermarket vouchers to reduce the risk of differential drop-out between study groups. Furthermore, we offer a small reimbursement of $20 to participants who engage with the process evaluation of phase 2 (peer-led blogs).

Study data will be stored on an encrypted drive to maintain confidentiality. The final trial dataset will be accessible by the investigation team. The Project Reference Group members who are external to the research team will function as the Data Monitoring Committee (DMC). The group is comprised on representatives from stakeholder organisations working in tobacco control in addition experts in mindfulness and goal setting interventions. The primary funder will nominate a representative for an observer-only role. The group will provide advice on the project’s feasibility and utility for stakeholder groups considering policy issues, translation of findings, and overall impact on low SES smokers. A formal DMC will not be established due to the minimal risk-levels of the interventions.

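### The protocol contradicts itself on whether the baseline survey precedes randomisation; if allocation comes first, the intention-to-treat set is selected after randomisation and no planned analysis covers everyone randomised

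*Protocol article*

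**What the plan says.** All references are to the protocol article.

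- **Screening and group allocation** runs through screening, consent, allocation, baseline questionnaire and forming of session groups, in that order. On allocation: "Participants will be randomly allocated to one of the three interventions or a control group using computerised sequence generation within the Qualtrics survey". The next sentence begins: "All participants will complete a baseline questionnaire (see Table 1").
- **Timepoints** says of the psychological and behavioural measures that they "will be measured before randomisation and then at 3 monthly intervals for the first 12 months".
- **Analyses** defines the set: "Our intention-to-treat population will be defined as all participants that were randomised and also completed the baseline survey". It also says "The main analyses will be performed on a per-protocol basis" and "We will perform a sensitivity analysis on a modified intention-to-treat basis and impute missing data where possible". On missing outcomes: "Missing smoking data will be presumed MNAR and analysed as continued smoking".
- **Discussion** relies on the modified intention-to-treat analysis to deal with attrition bias, and limits requests for data to people who completed the baseline survey.
- **Ethical considerations** offers intervention-arm participants (the figure is in dollars) "50 gift cards upon completion of the baseline survey and attendance at their first small group session". Control participants are offered lotteries that depend on completing the study; nothing is stated for them at baseline.
- **Equanimity** restricts that scale to the two mindfulness arms, and Timepoints has it measured at baseline.

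**The concern.** An intention-to-treat set should be fixed by randomisation. If people are allocated first and then have to complete a survey to be counted, the set depends on something that happens after allocation. The main analysis is per protocol, so the modified intention-to-treat analysis is the only stated protection against selective loss, and it would share the weakness.

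The rule that missing smoking status counts as smoking does not help these people, because they leave the set before the rule applies. Since no data are requested from them, their outcomes cannot be recovered later.

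If participants also know their arm at that stage, completion could differ between arms, and the 6-month comparison in this set would carry that difference.

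**Working it through.** **1. The plan's own figures.** Sample size and power analysis gives 25.2% and 13.6%, 80% power and two-sided alpha 0.05. With pooled variance under the null and mean rate 0.194:

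n = [1.960 × √(2 × 0.194 × 0.806) + 0.842 × √(0.252 × 0.748 + 0.136 × 0.864)]² / 0.116² = (1.096 + 0.466)² / 0.01346 ≈ 181.2, so 182 per group.

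182 / 0.9 = 202.2, so 203; 4 × 203 = 812. The stated figures reproduce, and this point does not change them.

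**2. The two orders side by side.**

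| Text | Allocation first | Survey first |
|---|---|---|
| Sequence in Screening and group allocation | fits | conflicts |
| Baseline condition in the intention-to-treat definition | excludes people | excludes nobody |
| Data requested only from baseline completers (Discussion) | has an effect | redundant |
| Measures taken before randomisation (Timepoints) | conflicts | fits |

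The arm-restricted equanimity baseline also suggests allocation first, but weakly. Timepoints dates that scale's later measurements from the start of phase 1, and it calls a week-5 goal assessment a baseline, so an arm-specific baseline need not be part of the common survey. Allocation first is the better supported reading, but it is not settled.

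**3. Possible size under allocation first.** The documents give no non-completion rate, so the following losses are assumptions. Suppose there is no treatment effect and 13.6% of all randomised are abstinent in both arms. Let m be the share of an arm that does not complete the baseline survey and q the abstinence rate among them. The rate among those analysed is

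(0.136 − m × q) / (1 − m).

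With q = 5%:
- m = 5%: (0.136 − 0.0025) / 0.95 = 14.05%
- m = 15%: (0.136 − 0.0075) / 0.85 = 15.12%
- spurious difference 1.07 points

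With q = 0, which is how the plan's missing-data rule would treat them:

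| m, arm A | m, arm B | Rate A | Rate B | B − A (points) |
|---|---|---|---|---|
| 5% | 10% | 14.3% | 15.1% | 0.8 |
| 5% | 15% | 14.3% | 16.0% | 1.7 |
| 5% | 20% | 14.3% | 17.0% | 2.7 |
| 10% | 10% | 15.1% | 15.1% | 0 |

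The difference favours the arm that loses more, because the people removed are assumed less likely to quit. Equal loss gives no spurious difference under the null. It does change the quantity estimated: at 10% loss in each arm and q = 0, the design difference becomes 0.252 / 0.9 − 0.136 / 0.9 = 28.0% − 15.1% = 12.9 points rather than 11.6.

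**4. Scale.** At 182 per arm and 13.6%, the standard error of a difference is √(2 × 0.136 × 0.864 / 182) = 3.6 points. The 5% against 15% cases are therefore about 0.3 standard errors (1.07 / 3.6) and 0.5 standard errors (1.7 / 3.6).

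**5. Is counting non-completers as smokers enough?** Keep q = 5% and losses of 5% and 15%. If non-completers are put back as smokers without being contacted, the rates are 0.136 − 0.0025 = 13.35% and 0.136 − 0.0075 = 12.85%. That is a spurious 0.5 points the other way, now favouring the arm with better completion. Redefining the set is not sufficient without asking these people for their outcome.

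**The case against.** The strongest reply is that Timepoints may describe what is done. The baseline condition is then redundant and the set is the randomised set. That cannot be excluded, which is why the finding is a contradiction to reconcile and not an established loss of randomised participants.

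A reader might go further and infer that the 50-dollar card makes controls drop out at baseline and so biases the trial. The documents do not support this, for three reasons.

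- The article places the randomiser inside the Qualtrics survey but does not say when the arm is disclosed. If disclosure follows the baseline survey, loss cannot respond to the arm, baseline scores cannot react to it, and dropping non-completers does not bias the comparison between arms.
- The card is tied jointly to the survey and to attending a first session, and it is described as compensation for data usage. The survey alone may earn nothing.
- If the card did raise completion in the intervention arms, controls would lose more. On the assumption that non-completers quit less, the bias would then run against the interventions.

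It is also fair to say that the affected set is a sensitivity analysis, labelled as modified, and that the illustrated bias is small beside the standard error. What remains is that the order is stated in two incompatible ways, and that on the better supported one no planned analysis includes everyone randomised.

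**Conclusion.** The point holds as a contradiction with a conditional consequence. Screening and group allocation and Timepoints cannot both be right about the order. The intention-to-treat condition and the limit on data requests favour allocation first. Under that order the set is selected on a post-randomisation event, those excluded are never followed, and the missing-equals-smoking rule never reaches them.

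Whether this biases the arm comparison depends on arm disclosure before the survey is finished, which is not stated. Size and direction are unknown. The figure of about 1 to 2 points for 5% against 15% loss rests wholly on assumed loss rates and on assumed abstinence of 0 to 5% among non-completers. It would be wrong to conclude that differential loss has occurred or that the results would favour the interventions.

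**What to change.** **Going forward.** Reconcile the two sections by placing the randomiser after the common baseline survey, as Timepoints states, so that everyone randomised has a baseline. Take the arm-specific equanimity baseline after allocation but before the first session.

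**For participants already randomised under the other order.** Recruitment began in May 2021 and this is the September 2022 version, so there may be many.
- Define intention-to-treat as all randomised, analysed as allocated.
- Remove the Discussion's restriction, so that 6-month smoking status is also requested from baseline non-completers.
- Count status that is still missing as smoking, and add a sensitivity analysis that varies this assumption.
- Report baseline completion by arm, and when allocation was disclosed.

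**Cost.** A change to the survey flow, short edits to three sections, some extra follow-up contacts, and a slightly lower abstinence rate in each arm because non-completers enter the denominator. If the survey flow does change during recruitment, participants will have been enrolled under two orders, and the report should say how many under each.
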